*D.3.3.1 Medical Record Abstraction* We will follow established guidelines and recommendations to insure complete and accurate chart abstractions[79-81]. All parts of the medical record will be reviewed including preventive medicine flow sheets (if present), progress notes, laboratory reports, and records from other providers. Chart reviews will be conducted by trained medical record abstractors. Training manuals for chart abstraction will be developed along with standardized training examples. To the fullest extent possible, chart abstractors will be blinded to the study hypothesis. To ensure reliability of chart reviews, the project director will re-abstract 20 charts for each medical record abstractor and calculate values of kappa for key variables. Values of kappa > 0.80 will be considered adequate evidence of reliability. Throughout the project the director will also similarly perform spot checks of medical record abstractor reliability. If values of kappa fall below this threshold corrective action and retraining will occur. Medical record abstractions will be conducted at primary care clinics, with additional abstractions of records obtained by all diagnostic, consulting, and treating facilities. Baseline data will be extracted for one year prior to clinic randomization to intervention arm.

Data will be entered on site using MedQuest, a software system for chart abstractions that is available free from the Centers for Medicare and Medicaid Services (<http://www.cms.hhs.gov/medquest>). The software system includes the ability to create data dictionaries and data entry rules, including enable/disable variables, enable/disable screens, validation rules, exit case rules, skip to, and save to rules. The rules provide the ability to restrict, enforce and validate the data that are being entered. Help screens are available through pop up windows. The program also allows data quality assessments, including comparisons between abstractors, and has data importing and exporting features. The variables to be abstracted are summarized in the following table.

| **Clinical data regarding abnormality** | ***Data Source*** |
| --- | --- |
| Initial abnormality – description (ex. Breast lump, abnormal mammogram) and date of onset | *Clinic record* |
| Date abnormality first addressed by primary provider | *Clinic record* |
| Diagnostic procedures performed (dates, results) | *Clinic record, outside records* |

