**D.4.4 Description of the Navigation Program**

The goal of the Navigator Program is to facilitate timely access to needed patient care interventions for patients exhibiting abnormal findings related to a breast or with a colorectal cancer screening abnormality. The principles that drive an effective navigation plan of intervention are based on patient/family assessment of needs, development and implementation of a plan of action and evaluation of outcomes. Additionally, a well- integrated Navigation Program with our partner agencies is needed to assure a seamless, well-coordinated program is established where the full scope of resources within the agencies, the cancer center and the community are utilized to meet patient needs. We envision that the navigator assigned at the community health center level will be well integrated into the existing site systems and well acquainted with community resources. The navigator will collaborate on a day-to-day basis with the health center interdisciplinary team, including health center outreach workers, financial advisors and clinical staff performing case management services.

Once a patient is enrolled in the study at a clinic randomized to provide the Navigator Program, the following activities become activated as part of the processes used to navigate the patient into and through the system. Simply put, the navigator helps the patient become informed about the various services, coordinates the care and assists them with decision-making tools. Key to the success of the navigator role is awareness of the availability of resources and creating meaningful and timely linkages. This role involves coordination of services, education and support offered in a highly personal and customized manner to help patients and families through this journey. The navigator provides an important access point to a wide array of services in a coordinated fashion that reduces the ‘shopping’ for providers and services. Specific tasks to be taken on by the patient navigator include the following:

- Effectively utilizes patient assessment tool to identify barriers to timely health services including transportation, health insurance funding, psycho-social needs, health education needs, child care needs, cultural or belief system barriers, unemployment, etc.

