**D.4.7.a** **Outcomes**

The primary outcome for this study is the time interval (in days) between abnormal finding suspicious for cancer and resolution. The onset of this time interval is the date of the abnormality meeting eligibility criteria *(Breast:* date that abnormal mammogram/US/MRI read by radiologist, date of abnormal clinical examination finding. *Colorectal:* date of abnormal screening [date sigmoidoscopy/colonoscopy performed, date FOBT interpreted], date that abnormal imaging test read by radiologist). If more than one abnormality meets eligibility criteria the onset of this time interval will begin with the earliest abnormality. Resolution is defined as the date that a definitive diagnosis is rendered regarding the initial abnormality. For breast, resolution may be indicated by definitive pathologic/cytologic findings (for women who undergo biopsy), definitive radiologic diagnosis, or by expert opinion (from breast surgeon). For colon, resolution will be defined by the date that pathologic interpretation of a biopsy specimen is rendered (if biopsy is performed) or by the date of diagnostic colonoscopy / radiologic imaging if no biopsy is performed. If more than one abnormality meets eligibility criteria resolution will be defined for the most clinically serious abnormality diagnosed (e.g. invasive cancer>>cancers in situ>>benign pathologic findings>>definitive radiological tests)

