**D.4.7.b Statistical Analysis and Study Power**

The statistical analyses will focus on those subjects receiving an abnormal or suspicious mammogram (BIRAD 0, 4, or 5) and those with abnormal FOBTs or abnormalities detected on sigmoidoscopy (see D.2.1). Those in the Navigator intervention groups will be compared to those in the control groups with respect to two outcomes. For patients with breast or colorectal abnormalities, the primary outcome will be time from detection of abnormality to definitive diagnosis, measured as a continuous variable. In addition, we will assess the proportion of patients who successfully complete an appropriate diagnostic evaluation. The records of each subject with such an indication for follow-up will be examined as described in D.3.3.

Study power is based on the following factors. The primary endpoint is ‘Length of time’ (LOT=time from screening to definitive diagnosis). Suppose LOT follows a normal distribution (mean=30 days, “std” = standard deviation). Then, to detect the difference in LOT between two groups (navigator versus control groups), a two-sample t-test will be used. The required minimum sample size to achieve 80% statistical power is calculated based on the t-test and illustrated in Figure 1.

For example, group sample sizes of 29 and 29 (total 58) achieve 80% power to detect a difference of 10 days between the null hypothesis that both group means are 30.0 and the alternative hypothesis that the mean of Navigator group is 20 days with estimated group standard deviations of 15.0 each and with a significance level of 0.05 using a one-sided two-sample t-test. However, to detect a difference of 5 days with the same standard deviation 15.0 between the two groups, one would need at least 112 samples for each group (total 224).

Figure 1. Required sample sizes for each group based on the expected mean of navigator group by the standard deviation. For the control group, the mean value of LOT was set up as 30.0. The standard deviations for both groups are assumed to be equal. α=0.05 (one sided: mean 1 > mean 2).

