Although we do not expect attrition of clinics, we have assessed power the possibility of between 6 and 8 participating clinics enrolling about 100 subjects each (a total of 600 - 800 subjects). Depending on the intracluster correlation coefficient (ICC) and the design effect, however, there may be effectively fewer subjects enrolled in this study from a statistical perspective. Assuming the intracluster correlation coefficient (ICC) to be in the range of 0.01 through 0.04, the effective sample sizes will be obtained as follows,

| # of total clinics | Actual Sample Sizes | ICC | Design Effect | Effected Sample Sizes |
| --- | --- | --- | --- | --- |
| 8 | 800 | 0.01 | 1.99 | 402 |
| 6 | 600 | 0.01 | 1.99 | 302 |
| 8 | 800 | 0.02 | 2.98 | 268 |
| 6 | 600 | 0.02 | 2.98 | 201 |
| 8 | 800 | 0.04 | 4.96 | 161 |
| 6 | 600 | 0.04 | 4.96 | 121 |

Therefore, given our expected sample sizes (600-800 subjects) even under the most conservative conditions (low design effects or ICC values, and relatively high population standard deviation), we will expect the desired statistical power will be achieved.

We will also conduct a number of secondary analyses in an exploratory fashion. For those with a suspicious screening result, we will compute the Kaplan-Meier curves for time from the suspicious result to definitive diagnosis (positive or negative) for each randomized arm. For those with positive diagnoses, we will compute Kaplan-Meier curves for time to onset of therapy for each randomized arm from both suspicious screening result and definitive diagnosis. In each case, we will estimate the standard error of these estimates with Greenwood’s formula and produce 95% confidence bands for these curves using the method of Hall and Wellner. The log rank test will be used to compare the two randomized groups. These comparisons will be at the two-sided 0.05 significance level.

Degree of adherence to NCCN standards will be assessed by an independent assessor blinded with respect to randomized arm and rated as 1 = complete adherence, 2 = substantial adherence, or 3 = poor adherence. The two randomized arms will be compared with respect to these adherence ratings using Wilcoxon’s Rank Sum Test.

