Risks: A concern could be raised that a loss of privacy could occur during the focus group (Phase I) if personal information is shared with others. In Phase II, the unit of randomization is at the clinic level and thus subjects in the control group will not be receiving the patient navigator intervention. However, patients at all clinics do receive follow-up and tracking of abnormalities through existing protocols according to their established standards of care. However, in consideration that this intervention could be efficacious, we do plan to offer the Patient Navigation Program to all sites after the initial evaluation has been conducted in the first two years. Thus, all patients at all sites will be exposed to the Patient Navigation Program at some point during the project.

Minimization: Within focus groups, all participants will be told at the start of the focus groups that information shared within the group should remain within the group. Subject data will be available only to research staff involved in this project. Data will be kept in locked filing cabinets in locked research rooms. Identifying information will not be reported. With regard to patients who are randomized to the control group, they will continue to receive standard care and outreach and follow-up, which is part of the standard protocols at the community-based centers. Once evaluated under controlled conditions, the Patient Navigation Program will be offered at all sites.

Risk: Exchange of information from one institution to another (Moffitt Cancer Center and the community-based centers).

Minimization: All data exchanged electronically from one institution to another and among team members will be in aggregate form with no identifiers.

Risk Chart abstractions conducted at six months or 12 months follow-up may identify patients for whom recommended care has not yet been received.

Minimization: Research assistants will compile listings of all patients for whom chart abstractions suggest that recommended care has not been received. These listings will be forwarded to the patient’s primary physician for review. Information that will be forwarded will include patient’s name, medical record number, and a listing of the targeted health services that were recommended but not received according to information obtained in the medical record abstraction.

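### Primary-outcome dates are abstracted on site by staff masked to the hypothesis but not to arm, which leaves room for arm-dependent dating, mainly in breast resolution without biopsy

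*Protocol*

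**What the plan says.** The abstraction procedure is in D.3.3.1 of the protocol. Its masking statement reads: "To the fullest extent possible, chart abstractors will be blinded to the study hypothesis". On place it says: "Medical record abstractions will be conducted at primary care clinics, with additional abstractions of records obtained by all diagnostic, consulting, and treating facilities". On scope: "All parts of the medical record will be reviewed including preventive medicine flow sheets (if present), progress notes, laboratory reports, and records from other providers". The variable table there lists, among other items, diagnostic procedures with dates and results, and one field for the date on which the abnormality received its definitive diagnosis.

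D.3.3 stands under Phase I baseline collection, but D.4.7.b extends it to the trial: "The records of each subject with such an indication for follow-up will be examined as described in D.3.3". D.4.5 prescribes the same chart abstraction, with the same outcome tables, for navigated and control subjects.

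On allocation, E.2.2 says: "In Phase II, the unit of randomization is at the clinic level". On the navigators, D.4.4 says: "We envision that the navigator assigned at the community health center level will be well integrated into the existing site systems".

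D.4.7.a defines the primary outcome as the days from the abnormal finding to its resolution. For breast, resolution may rest on pathology or cytology, or on "definitive radiologic diagnosis, or by expert opinion (from breast surgeon").

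One outcome does have masking to arm. In D.4.7.b, adherence to NCCN standards "will be assessed by an independent assessor blinded with respect to randomized arm".

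**The concern.** The protocol applies a stronger safeguard to a secondary rating than to the primary outcome. An abstractor who sits in a clinic of one arm and reads the whole chart, progress notes included, will probably meet signs of navigation. If that person must also decide on which day a non-biopsied breast abnormality was settled, the decision can lean one way in one arm.

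Such a shift would enter the treatment difference directly. A larger sample does not shrink it; the shift only becomes easier to declare significant. Because D.4.7.b sizes the trial on a one-sided test in favour of navigation, a shift in that direction would act wholly on the false-positive rate.

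**Working it through.** **Step 1. Does the masking statement reach the primary outcome?** Yes, through the cross-reference in D.4.7.b. Without it, D.3.3.1 would concern only data from the year before a clinic was randomised, when arm does not matter.

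**Step 2. Is the arm visible to the abstractor?** The protocol does not say that abstractors are told it. Clinic-level allocation, on-site abstraction, whole-chart review and navigators based in the health centers together make knowledge of arm likely.

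**Step 3. Which dates leave discretion?** From D.4.7.a:
- Start dates are tied to events: the day imaging was read, the day of the abnormal examination, the day of endoscopy, the day the FOBT was interpreted. With several abnormalities, the earliest counts.
- Colorectal end dates are the pathology date or, without biopsy, the date of diagnostic colonoscopy or imaging.
- Breast end dates with biopsy follow the pathology or cytology findings.
- With several abnormalities, a seriousness order is printed, from invasive cancer down to definitive radiological tests. It is given by way of example and has no place for a surgeon's opinion.
- Breast end dates without biopsy depend on when a radiologic diagnosis is definitive or a surgeon's opinion settles the matter. This is the main area of discretion, and the abstracted field holds a single date.

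**Step 4. Would the planned check detect a shift?** The project director re-abstracts 20 charts per abstractor and requires kappa above 0.80. The director is not stated to be masked to arm. Kappa measures agreement, so two readers who lean the same way will agree.

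**Step 5. Size, as an illustration only.** The plan's own figures reproduce first. With SD 15, one-sided alpha 0.05 and 80% power, the normal formula n = 2 × SD² × (1.645 + 0.842)² / d² gives 112 per group for d = 5 days and 28 for d = 10. The exact t-test gives 112 and 29, as stated. The design effect 1 + 99 × ICC gives 1.99 at ICC 0.01 (800 / 1.99 = 402 effective subjects) and 4.96 at ICC 0.04 (600 / 4.96 = 121), also as stated.

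Now assume that a share f of all end dates is recorded s days too early in the navigator arm, and that there is no true effect. The mean shift is b = f × s. With n per group equal to half the effective total, the one-sided false-positive rate is Φ(b / (15 × √(2/n)) − 1.645). The standard error 15 × √(2/n) is 2.727 days at 121 effective subjects (n = 60.5) and 1.496 days at 402 (n = 201).

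| f | s (days) | b (days) | b / 5 days | Rate, 121 | Rate, 402 |
|---|---|---|---|---|---|
| 0.1 | 3 | 0.3 | 6% | 6% | 7% |
| 0.3 | 2 | 0.6 | 12% | 8% | 11% |
| 0.3 | 5 | 1.5 | 30% | 14% | 26% |
| 0.6 | 5 | 3.0 | 60% | 29% | 64% |

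For example, with b = 1.5 and 402 effective subjects: 1.5 / 1.496 − 1.645 = −0.642, and Φ(−0.642) = 0.26. No value of f or s comes from the protocol.

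**The case against.** The strongest reply is that little is left to the abstractor. D.4.7.a ties starts to events, names the earliest abnormality as the onset, prints a seriousness order and leaves no colorectal end date open. Even for breast without biopsy, the abstractor mainly copies another clinician's dated decision. This stands, and it confines the point to a subset of one cancer site. A reader might infer that the primary outcome as a whole is a subjective rating; the document does not support that.

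Second, knowledge of arm is inferred. A directional shift also requires an abstractor who knows which direction is wanted, and masking to the hypothesis is aimed at exactly that. This stands in part. The masking has some value, but it is promised only as far as possible, and it is hard to sustain where the navigator is part of the clinic.

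Third, the NOVA Data Dictionary and the abstraction training manuals are not shown and may define the dates more tightly. That is possible. It would narrow the discretion but would not mask anyone to arm, and the protocol itself sets what is masked.

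Fourth, D.3.3.1 already collects procedure dates and results and provides validation rules and spot checks. This is correct, and it is why the remedy is cheap.

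Fifth, the NCCN assessor is planned for one task only, and nothing shows capacity for more. This stands, so the remedy should not depend on that person.

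**Conclusion.** The point holds in limited form. The people who supply the primary-outcome dates are masked to the hypothesis only and probably know the arm, while a secondary rating is masked to arm. The exposure is mainly breast resolution without biopsy. The conclusion rests on the cross-reference in D.4.7.b and on the inference that on-site work reveals the arm.

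Bias is possible, not shown, and the protocol gives no basis for its size or direction. A reader might take the shifts of 0.3 to 3.0 days, or the false-positive rates of 6% to 64%, as properties of this trial. They are not: they follow from assumed shares, shifts and direction, and show only that a small systematic lean would matter against a 5-day difference. This is a worthwhile, inexpensive improvement and does not invalidate the primary outcome.

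**What to change.** In D.3.3.1 and D.4.7:
1. Have abstractors record every qualifying abnormality, procedure, report date and opinion date with its result and source, in place of one chosen definitive-diagnosis date. Much of this is collected already.
2. Derive start and end dates centrally with a fixed program that applies the D.4.7.a rules to a file without clinic or arm.
3. Where the program cannot settle a non-biopsy breast resolution, have someone masked to arm assign the date from the abstracted entries, with clinic, arm and navigator references removed. The NCCN assessor could do this if capacity allows.
4. State that date assignment is masked to arm.

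The cost is a derivation program, somewhat fuller abstraction and limited review time for unresolved cases. On-site abstraction can stay. The patient-level file must be squared with E.2.2, which restricts electronic exchange to aggregate data; D.4.7.b already foresees monthly transfer of the study database to the biostatistician, so the two sections need reconciling in any case.

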### **D.3.4 Recruitment and Training of Navigators**

Patient navigators will be recruited through the community-based centers and our community partners. Personal characteristics important when hiring navigators and consistent with the Freeman model[22] include: being culturally attuned to the community; knowledgeable about community systems and resources; having strong problem-solving abilities; being able to connect with required systems that impact funding sources; and being cultural competent (See Appendix for proposed job description). The patient navigators will undergo extensive training under the guidance of an interdisciplinary academic-community team including [name], [name], [name], [name] and our community partners (Suncoast, Tampa Community Health Center and Health Choice) in Phase I. We will provide an initial three-day training seminar for newly recruited navigators from our partner community-based health and social service agencies to enhance the skills and capacity to effectively implement the Navigation Program. The three-day training program will include didactic, group, role-playing and actual fieldwork, and be based on adult learning principles. This training will include instruction in how to implement the navigator protocol with patients as well as instruction in how to interact with health care professionals to promote delivery of timely high quality care to patients being navigated. Navigators will also receive information about resources available to help patients with regard to practical, financial, and emotional concerns. Case studies will be reviewed and problem-solving and skill-building techniques in navigation will be emphasized. Critical to this aspect of the training is understanding linkages to key medical stakeholders and processes to achieve successful navigation. As part of the training, each navigator will be audiotaped delivering key elements of the intervention to a limited number of patients not participating in the randomized trial. Audiotapes will be reviewed by [name] and her team who will provide feedback individually to each navigator. During the course of the study, 20% of each navigator’s initial and follow-up contacts with participants will be recorded. The audiotapes will be reviewed by [name] and [name] who will provide feedback to each navigator about any possible drift from the original intervention protocols while recognizing the need for customized and personalized care. Feedback will be provided during regularly scheduled meetings, (biweekly) at which time [name] and the lead navigator will review with each navigator any issues and problems that may be occurring in the delivery of the intervention. Bi-weekly meetings will be held with the navigators to boost skills, camradarie and encourage problem-solving skills.
